#### 7.1.2 Secondary study parameters/endpoints (if applicable)

- Difference in core body temperature before and after metformin use and the correlation with  $^{18}\text{F}$ -FDG uptake in the colon.
- Difference in energy expenditure before and after metformin use and the correlation with  $^{18}\text{F}$ -FDG uptake in the colon.
- Correlation between difference in core temperature and respectively  $^{18}\text{F}$ -FDG uptake in the colon and energy expenditure, before, after 7 days of daily metformin use.
- Difference in lactate, before and after the use of metformin and the correlation between lactate and respectively  $^{18}\text{F}$ -FDG uptake in the colon, core body temperature and energy expenditure.

#### 7.1.3 Other study parameters (if applicable)

### 7.2 Study procedures

All included subjects will be asked about their medical history and undergo a brief physical examination (vital signs) at the screening visit. A detailed description of the study procedures has been given in the 'Study Design' section. Below you will find an overview of the invasive study procedures.

Invasive procedures:

- Blood sampling for laboratory test: liver function, kidney function
- 2 Placements of an intravenous canula at *visit 1*, 2 blood sampling for laboratory test: plasma glucose, insulin and lactate
- Taking the body core temperature pill
- $^{18}\text{F}$ -FDG PET-CT

Total amount of blood drawn during study: 60 ml

### 7.3 Withdrawal of individual subjects

Subjects can leave the study at any time for any reason if they wish to do so without any consequences. The investigator can decide to withdraw a subject from the study for urgent medical reasons.

### **7.3.1 Specific criteria for withdrawal (if applicable)**

### **7.4 Replacement of individual subjects after withdrawal**

Subjects withdrawn during completion of the study will be replaced.

### **7.5 Follow-up of subjects withdrawn from treatment**

All subjects who were withdrawn from the study for medical reasons, will be followed up by the investigator until their care can be transferred to their own physician.

### **7.6 Premature termination of the study**

There are no reasons to terminate this study premature.

## 8. SAFETY REPORTING

### 8.1 Section 10 WMO event

In accordance to section 10, subsection 1, of the WMO, the investigator will inform the subjects and the reviewing accredited METC if anything occurs, on the basis of which it appears that the disadvantages of participation may be significantly greater than was foreseen in the research proposal. The study will be suspended pending further review by the accredited METC, except insofar as suspension would jeopardise the subjects' health. The investigator will take care that all subjects are kept informed.

### 8.2 AEs, SAEs and SUSARs

#### 8.2.1 Adverse events (AEs)

Adverse events are defined as any undesirable experience occurring to a subject during the study, whether or not considered related to metformin. All adverse events reported spontaneously by the subject or observed by the investigator or his staff will be recorded.

#### 8.2.2 Serious adverse events (SAEs)

A serious adverse event is any untoward medical occurrence or effect that at any dose:

- results in death;
- is life threatening (at the time of the event);
- requires hospitalisation or prolongation of existing inpatients' hospitalisation;
- results in persistent or significant disability or incapacity;
- is a congenital anomaly or birth defect;
- Any other important medical event that may not result in death, be life threatening, or require hospitalization, may be considered a serious adverse experience when, based upon appropriate medical judgement, the event may jeopardize the subject or may require an intervention to prevent one of the outcomes listed above.

The sponsor will report the SAEs through the web portal *ToetsingOnline* to the accredited METC that approved the protocol, within 15 days after the sponsor has first knowledge of the serious adverse events.

SAEs that result in death or are life threatening should be reported expedited. The expedited reporting will occur not later than 7 days after the responsible investigator

has first knowledge of the adverse event. This is for a preliminary report with another 8 days for completion of the report.

### 8.2.3 Suspected unexpected serious adverse reactions (SUSARs)

Adverse reactions are all untoward and unintended responses to an investigational product related to any dose administered.

Unexpected adverse reactions are SUSARs if the following three conditions are met:

1. the event must be serious (see chapter 9.2.2);
2. there must be a certain degree of probability that the event is a harmful and an undesirable reaction to the medicinal product under investigation, regardless of the administered dose;
3. the adverse reaction must be unexpected, that is to say, the nature and severity of the adverse reaction are not in agreement with the product information as recorded in:
  - Summary of Product Characteristics (SPC) for an authorised medicinal product;
  - Investigator's Brochure for an unauthorised medicinal product.

The sponsor will report expedited the following SUSARs through the web portal *ToetsingOnline* to the METC:

- SUSARs that have arisen in the clinical trial that was assessed by the METC;
- SUSARs that have arisen in other clinical trials of the same sponsor and with the same medicinal product, and that could have consequences for the safety of the subjects involved in the clinical trial that was assessed by the METC.

The remaining SUSARs are recorded in an overview list (line-listing) that will be submitted once every half year to the METC. This line-listing provides an overview of all SUSARs from the study medicine, accompanied by a brief report highlighting the main points of concern.

The expedited reporting of SUSARs through the web portal *ToetsingOnline* is sufficient as notification to the competent authority.

The sponsor will report expedited all SUSARs to the competent authorities in other Member States, according to the requirements of the Member States.

The expedited reporting will occur not later than 15 days after the sponsor has first knowledge of the adverse reactions. For fatal or life threatening cases the term will be maximal 7 days for a preliminary report with another 8 days for completion of the report.

### **8.3 Annual safety report**

In addition to the expedited reporting of SUSARs, the sponsor will submit, once a year throughout the clinical trial, a safety report to the accredited METC, competent authority, and competent authorities of the concerned Member States.

This safety report consists of:

- a list of all suspected (unexpected or expected) serious adverse reactions, along with an aggregated summary table of all reported serious adverse reactions, ordered by organ system, per study;
- a report concerning the safety of the subjects, consisting of a complete safety analysis and an evaluation of the balance between the efficacy and the harmfulness of the medicine under investigation.

### **8.4 Follow-up of adverse events**

All AEs will be followed until they have abated, or until a stable situation has been reached. Depending on the event, follow up may require additional tests or medical procedures as indicated, and/or referral to the general physician or a medical specialist. SAEs need to be reported till end of study within the Netherlands, as defined in the protocol

## 9. STATISTICAL ANALYSIS

The baseline characteristics of all subjects will be outlined in a table describing variables such as age, BMI and HOMA-index. The differences in these characteristics before and after the use of metformin will be determined using the mann whitney u test.

### 9.1 Primary study parameter(s)

P-values for the difference in  $^{18}\text{F}$ -FDG uptake in the colon before and after using metformin will be determined using the mann whitney u test.

Differences between lean and obese subjects will also be determined using the mann whitney u test.

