### 3. STUDY DESIGN

In this non-randomised intervention study we will study the influence of metformin (1000 mg/day (500 mg in the morning, 500 mg in the evening) during 1 week) on  $^{18}\text{F}$ -FDG uptake in the colon. The main outcome will be difference in  $^{18}\text{F}$ -FDG uptake. Furthermore, we will measure core body temperature, energy expenditure and HOMA-index. 16 healthy volunteers of Caucasian origin will be included (8 lean, BMI < 24 kg/m^2 and 8 obese BMI > 28 kg/m^2) in this study. Subjects (n=16) will be investigated before and after using metformin (1000 mg/day during 1 week). Included subjects will visit the AMC hospital on three occasions. Below is a description of each visit.

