#### 4.4 Sample size calculation

Based on a retrospective study we have recently performed,[[name], EASD 2014] we aim to find an increase in SUV of 2,8 g/L in the colon. This is an increase from grade 1 to grade 3 based on a visual scale designed by Gontier et al. A sample size of 8 will have 80% power to detect a difference in means of 2,8 (e.g. a First condition mean of 2,7 SUV and a Second condition mean of 5,5 SUV), assuming a standard deviation of differences of 2,24, using a paired t-test with a 0,05 two-sided significance level. To allow for unexpected findings and to increase power we will include 11 subjects per arm.

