## 7. METHODS

### 7.1 Study parameters/endpoints

#### 7.1.1 Main study parameter/endpoint

Difference in  $^{18}\text{F}$ -FDG uptake as registered by  $^{18}\text{F}$ -FDG PET-CT before and after 7 days of daily metformin use.

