### 9.2 Secondary study parameter(s)

P-values for the difference in core body temperature, energy expenditure, HOMA-index and lactate concentration before and after using metformin will be determined using the mann whitney u test.

Differences between lean and obese subjects will also be determined using the mann whitney u test.

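### Every before/after comparison is assigned the Mann-Whitney U test, an independent-samples test, although the data are paired and the 80% power was calculated for a paired t-test

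*Protocol*

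**What the plan says.** The design is within-subject. Protocol Section 3 states that the men "will be investigated before and after using metformin (1000 mg/day during 1 week", and Section 7.1.1 defines the main endpoint as the difference in uptake on "PET-CT before and after 7 days of daily metformin use".

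Section 4.4 plans for that design. It states that "A sample size of 8 will have 80% power to detect a difference in means of 2,8", "assuming a standard deviation of differences of 2,24", and "using a paired t-test with a 0,05 two-sided significance level".

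Section 9 then names a different kind of test:

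- Section 9.1, primary endpoint: P-values for 18F-FDG "uptake in the colon before and after using metformin will be determined using the mann whitney u test".
- Section 9.2, for core temperature, energy expenditure, HOMA-index and lactate: the difference "before and after using metformin will be determined using the mann whitney u test".
- Section 9, opening paragraph, for the baseline characteristics: "The differences in these characteristics before and after the use of metformin will be determined using the mann whitney u test".

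Sections 9.1 and 9.2 each add a second sentence giving the same test to the comparison of lean with obese men. No paired test appears anywhere in Section 9.

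**The concern.** The Mann-Whitney U test compares two independent groups. Its null distribution assumes that every value in one sample is independent of every value in the other. Here the two samples are the same men on two occasions, so that assumption fails unless a man's two values happen to be uncorrelated. The test discards the pairing and counts the stable differences between men as noise, which a paired analysis would remove.

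Two things are at stake. The P-values for the primary endpoint and for all before/after secondary comparisons would not have the error rate attached to them. And the power statement in Section 4.4 belongs to a test that Section 9 does not use, so a reader cannot tell what power the planned analysis has.

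**Working it through.** **Inputs from Section 4.4.** Mean difference 2.8 SUV (2.7 before, 5.5 after), SD of within-man differences 2.24, two-sided alpha 0.05, n = 8.

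**Reproducing the plan's figure.** The standardised difference is 2.8/2.24 = 1.25. For the paired t-test the noncentrality is 1.25 × √n with n − 1 degrees of freedom.

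- n = 7: power 78.6%.
- n = 8: noncentrality 1.25 × √8 = 3.54, power 85.6%.

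So 8 is the smallest n that reaches 80%, and the stated sample size is correct for the paired t-test. An exact Wilcoxon signed-rank test on normal differences has simulated power of about 80.0% at n = 8. Neither figure depends on the before/after correlation, because both tests use only the differences.

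**Power of the test that Section 9 names.** This does depend on the correlation ρ, which the protocol does not give. Assume normal data with the same SD, σ, at both visits. The variance of a difference is then 2σ²(1 − ρ). Holding the SD of differences at 2.24 gives σ = 2.24/√(2(1 − ρ)):

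- ρ = 0: σ = 2.24/√2.0 = 1.58, so 2.8/σ = 1.77
- ρ = 0.3: σ = 2.24/√1.4 = 1.89, so 2.8/σ = 1.48
- ρ = 0.5: σ = 2.24/√1.0 = 2.24, so 2.8/σ = 1.25
- ρ = 0.7: σ = 2.24/√0.6 = 2.89, so 2.8/σ = 0.97

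The unpaired test sees the last figure in each line, which shrinks as ρ rises. Simulating the exact two-sided Mann-Whitney test on such pairs (at least 20,000 replicates per cell) gives the results below. The sizes are the 8 per group of Section 3, the 11 per arm of Section 4.4, and the 8 + 8 = 16 men pooled.

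| ρ | Type I error, n = 8 | Power, n = 8 | Power, n = 11 | Power, n = 16 |
|---|---|---|---|---|
| 0 | about 5% | 89% | 97% | over 99% |
| 0.3 | about 2% | 79% | 92% | 99% |
| 0.5 | about 1% | 66% | 83% | 96% |
| 0.7 | about 0.3% | 41% | 60% | 84% |
| Paired t-test, any ρ | 5% | 85.6% | 96.1% | 99.7% |
| Signed-rank, any ρ | 3.9% (exact level) | 80% | 95% | 99% |

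Mann-Whitney power drops below 80% at ρ of about 0.3 for n = 8, about 0.55 for n = 11 and about 0.7 for 16 pooled. If the correlation were negative the error would run the other way: at ρ = −0.3 and n = 8 the true type I error is 8.6%.

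**The case against.** **It may be a slip of naming.** The authors may have meant the signed-rank test, and at ρ = 0 nothing is lost. But the wording occurs three times and nothing in the protocol points to the signed-rank test. Nor can the sentences mean Mann-Whitney applied to the changes, because one set of changes is a single sample and the lean/obese comparison has its own sentence.

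**A reader might infer that the study does not have 80% power.** The protocol does not support that without conditions. No correlation is stated. At n = 8 the planned test still reaches 80% for ρ below about 0.3, and the primary objective covers lean and obese men together. If all 16 are analysed together, power at ρ = 0.5 is 96%.

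**A reader might extend the table to higher correlations.** At ρ = 0.9 the same model gives 7% power at n = 8, but it needs σ = 2.24/√0.2 = 5.0 around a baseline mean of 2.7. That puts about 29% of baseline SUV values below zero, which is impossible, so the row is not used. The 0.7 row is already strained, with σ = 2.89 and about 18% below zero, and should be read as an upper end.

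**A reader might infer a collapse of power for the secondary endpoints.** The test is equally wrong there, but the protocol gives no effect size or SD for any of them, so the loss cannot be quantified.

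**A reader might fear false positive findings.** Under positive correlation the test is conservative. The harm is lost power and miscalibrated P-values, not excess type I error.

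The absence of effect estimates with intervals from Section 9 is not part of this point, since an analysis plan may supply them.

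**Conclusion.** The test named for the primary endpoint, and for every other before/after comparison, is wrong for the design and contradicts Section 4.4. This holds at any sample size and needs no assumption beyond the protocol's own description of the data.

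The consequence for power is conditional. The stated 80% is not supported for the planned test. Whether it is lost depends on a correlation that the protocol does not give and on the number of men analysed, which Sections 3 and 4.4 give differently. The power and type I error figures further assume normal data, equal SDs at both visits and an SD of differences of 2.24.

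The point should be corrected before analysis, because it decides whether the primary P-value means what it says.

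**What to change.** In Sections 9, 9.1 and 9.2, replace the Mann-Whitney U test for every before/after comparison by the Wilcoxon signed-rank test on the within-man differences, or by the paired t-test already named in Section 4.4. Either one supports the stated 80% at n = 8 on the protocol's inputs. Name the chosen test in Section 4.4 as well, so that the power statement and the analysis refer to the same test. Keep Mann-Whitney only for comparing lean with obese men, where the groups are independent.

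The cost is a change of wording. No further subjects, visits or measurements are needed.

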### 9.2 Secondary study parameter(s)

P-values for the difference in core body temperature, energy expenditure, HOMA-index and lactate concentration before and after using metformin will be determined using the mann whitney u test.

Differences between lean and obese subjects will also be determined using the mann whitney u test.

### 9.3 Other study parameters

Correlations between  $^{18}\text{F}$ -FDG uptake and 1) core body temperature, 2) energy expenditure, 3) HOMA-index and 4) lactate concentration will be determined using Spearmans correlation coefficient.

### 9.4 Interim analysis (if applicable)

None

## **10. ETHICAL CONSIDERATIONS**

### **10.1 Regulation statement**

The study will be conducted according to the principles of the Declaration of Helsinki (Fortaleza, Brazil, October 2013) and in accordance with the Medical Research Involving Human Subjects Act (WMO) and CCMO guidelines

### **10.2 Recruitment and consent**

The healthy volunteers will be recruited by advertisement in a local paper and at the medical faculty of the AMC. When the volunteers contact the study team they will receive additional information about the study and the informed consent procedure will be performed at the screening visit by the research physician [name]. The patient information letter and informed consent form are attached as a separate document. Subjects have access to an independent physician to discuss their participation. They are informed about this opportunity in the patient information letter.

### **10.3 Objection by minors or incapacitated subjects (if applicable)**

No minors or incapacitated subjects will be included in this study

### **10.4 Benefits and risks assessment, group relatedness**

Both obesity and type 2 diabetes are growing worldwide problems. Complications associated with obesity not only cause a high mortality, but also increase health costs. At present, interventions such as diets, sports training, behavioural therapy and pharmacological therapy achieve disappointing and often temporary results. The potential of the colon to function as energy dissipating organ could be a new target in the treatment of obesity. The thermogenic properties of the gut have never been explored and it is a new and exciting concept which warrants investigation.

### **10.5 Compensation for injury**

The sponsor/investigator has a liability insurance which is in accordance with article 7, subsection 9 of the WMO.

The sponsor (also) has an insurance which is in accordance with the legal requirements in the Netherlands (Article 7 WMO and the Measure regarding Compulsory Insurance for Clinical Research in Humans of 23th June 2003). This insurance provides cover for damage to research subjects through injury or death caused by the study.

1. € 450.000,-- (i.e. four hundred and fifty thousand Euro) for death or injury for each subject who participates in the Research;
2. € 3.500.000,-- (i.e. three million five hundred thousand Euro) for death or injury for all subjects who participate in the Research;
3. € 5.000.000,-- (i.e. five million Euro) for the total damage incurred by the organisation for all damage disclosed by scientific research for the Sponsor as 'verrichter' in the meaning of said Act in each year of insurance coverage.

The insurance applies to the damage that becomes apparent during the study or within 4 years after the end of the study.

#### **10.6 Incentives (if applicable)**

All subjects included in this study will receive 230 euro for participating in this study and will receive 0,12 euro/kilometre travelling expenses.

## ADMINISTRATIVE ASPECTS, MONITORING AND PUBLICATION

### 10.7 Handling and storage of data and documents

Each subject will receive a specific subject identification number. The subject will be identified by this number for the duration of the trial. All the participating investigators have access to the source data. Blood samples for analysis and storage will be labelled with this code and visit number. Data will be kept for at least 20 years.

### 10.8 Amendments

*<The following text is applicable for studies without an investigational medicinal product.>*

Amendments are changes made to the research after a favourable opinion by the accredited METC has been given. All amendments will be notified to the METC that gave a favourable opinion.

All substantial amendments will be notified to the METC and to the competent authority. Non-substantial amendments will not be notified to the accredited METC and the competent authority, but will be recorded and filed by the sponsor.

### 10.9 Annual progress report

The sponsor/investigator will submit a summary of the progress of the trial to the accredited METC once a year. Information will be provided on the date of inclusion of the first subject, numbers of subjects included and numbers of subjects that have completed the trial, serious adverse events/ serious adverse reactions, other problems, and amendments.

### 10.10 End of study report

The sponsor will notify the accredited METC of the end of the study within a period of 90 days. The end of the study is defined as the last patient's last visit.

In case the study is ended prematurely, the sponsor will notify the accredited METC within 15 days, including the reasons for the premature termination.

Within one year after the end of the study, the investigator/sponsor will submit a final study report with the results of the study, including any publications/abstracts of the study, to the accredited METC.

**10.11 Public disclosure and publication policy**

This is an investigator driven study. Data will be published without restrictions by any sponsor

## 11. STRUCTURED RISK ANALYSIS

### 11.1 Potential issues of concern

#### a. Level of knowledge about mechanism of action

See SPC page 6 and 7

#### b. Previous exposure of human beings with the test product(s) and/or products with a similar biological mechanism

Metformin is used for many years, the use of metformin has been considered as very safe. See SPC page 5 and 6.

#### c. Can the primary or secondary mechanism be induced in animals and/or in ex-vivo human cell material?

The use of metformin is considered as very safe. Furthermore, animal data is not always easy to translate to human data. Since 88% of the subjects using metformin show a high F-FDG-uptake in the colon in our retrospective study, we only need a small number of participants to analyze the potential mechanism.

